### Therapists and training

Before participation in the trial, master’s level therapists attend a two-day training in prolonged exposure and a two-day training in STAIR. At the end of these trainings, the therapists have to pass an exam with pilot patients, which is graded by the supervisors of the study. During the study, all therapists receive weekly supervision in (i)PE (by AM and RK) and PBT (by MC and IW). All treatment locations offer the three types of treatment and all therapists receive the same amount of supervision and training. Adherence to the treatment protocols will be checked by independent observers, who will rate randomly selected videotaped therapy sessions.

### Prolonged exposure therapy

Prolonged exposure therapy (PE) is delivered in 16 weekly sessions of 90 min. The treatment manual is based on the PE protocol by Foa, Hembree, & Rothbaum (2007) [50].

Treatment sessions consist of imaginal exposure (repeated recounting of the most anxiety provoking traumatic memories and processing related thoughts and feelings), and exposure in vivo (approaching trauma-related situations). Between sessions, participants listen to audio recordings of the imaginal exposure on a daily basis, and complete in-vivo homework assignments.

### Intensified prolonged exposure therapy

Intensified prolonged exposure therapy (iPE) involves three weekly sessions of 90 min PE for a period of four weeks (12 sessions total), followed by two PE sessions after one and two months (14 sessions total). The same protocol is used as in the PE condition with some minor changes for practical considerations. For instance, when two treatment sessions are given on consecutive days patients are instructed to do combined homework of both sessions. After the first 12 sessions, patients are instructed to keep doing imaginal exposure and exposure in vivo homework for the 13th and 14th sessions. For practical considerations, two therapists deliver the iPE sessions alternately.

### Phase-based therapy

Phase-based therapy (PBT) is delivered in 8 weekly 60 min STAIR sessions [51], followed by 8 weekly 90 min PE sessions. STAIR is a manualized skills training, adapted from dialectical behavior therapy and cognitive behavioral therapy [52]. The first four STAIR sessions focus on improving emotion regulation skills, including labeling and identifying feelings, emotion management, distress tolerance and the acceptance of feelings and experiencing positive emotions. The last four STAIR sessions focus on developing interpersonal skills and address exploration and revision of maladaptive schemas, the conflict between trauma generated feelings and interpersonal goals in the present, differences in power and control and flexibility in interpersonal situations with differences in power [31]. Throughout the treatment, patients receive psychoeducation, especially about the connection between the traumatic events during their childhood and the effect it has on their present thoughts, feelings and behavior. After these eight sessions the protocol continues with the standard PE protocol [50]. This differs from the standard STAIR protocol, which continues with the Narrative Story Telling (NST) protocol [53].

### Instruments

In Table 1, an overview is presented of all the included measures and measurement points.

**Table 1 Tab1:** Overview of the measurements per time point

Clinical interview	Construct	T0	T1	T2	T3	T4	T5
MINI	Axis-1 disorders	X			X	X	X
CAPS-5	PTSD	X	X	X	X	X	X
CPI	Complex PTSD	X	X	X	X	X	X
SCID II	Personality disorders	X				X	
DSP-I	Dissociation	X	X	X	X	X	X
Self-report							
Demographics	Demographics	X					
LEC-5	Traumata	X					
CTQ	Childhood maltreatment	X				X	
PCL-5^b^	PTSD symptoms	X	X	X	X	X	X
DERS^b^	Emotion regulation	X	X	X	X	X	X
ICD-11	Complex PTSD	X	X	X	X	X	X
BDI-II	Depression	X	X	X	X	X	X
PTCI	Posttraumatic cognitions	X	X	X	X	X	X
DES	Dissociation	X	X	X	X	X	X
SDQ-5	Somatoform Dissociation Questionnaire	X	X	X	X	X	X
DERS	Emotion regulation	X	X	X	X	X	X
TIC-P	Direct/indirect costs	X			X	X	X
IIP	Interpersonal problems	X	X	X	X	X	X
MOS	Social support	X	X	X	X	X	X
RSES	Self-esteem	X	X	X	X	X	X
ZAV	Anger	X	X	X	X	X	X
ACS	Attentional control	X	X	X	X	X	X
LEIDS	Cognitive reactivity				X		
Treatment credibility	Treatment credibility	X			X		
Treatment Goals	Treatment goals	X					
EQ-5L5D	Quality of life	X	X	X	X	X	X
WAI^a^	Working alliance						
Cognitive task							
Avoidance task	Avoidance behavior	X					
Process variables		Measurement moment					
HE	Harm expectancies	Prior and after (imaginal) exposure					
SUD	Subjective distress	Multiple times during (imaginal) exposure					

*MINI* Mini-international Neuropsychiatric Interview, *CAPS-5* Clinician Adminstered PTSD Scale, *CPI* Complex PTSD Items, *SCID II* Structured Clinical Interview for DSM-IV axis-II personality disorders, *DSP-I* Dissociatief Subtype van PTSS, *LEC-5* Life Events Checklist for DSM-5, *CTQ* Childhood Trauma Questionnaire, *PCL-5* PTSD Checklist for DSM-5, *DERS* Difficulties in Emotion Regulation Scale, *ICD-11* International Classiciation of Diseases-11, *BDI-II* Beck Depression Inventory-II, *PTCI* The posttraumatic cognitions inventory, *DES* Dissociative Experiences Scales, *SDQ-5* Somatoform Dissociation Questionnaire-5, *DERS* Difficulties in Emotion Regulation Scale; *TIC-P* Trimbos and iMTA questionnaire on Costs associated with Psychiatric illness, *IIP* Inventory of Interpersonal Problems, *MOS* Medical Outcomes Study, *RSES* Rosenberg Self-Esteem Scale, *ZAV* Zelf Analyse Vragenlijst, *ACS* Attentional Control Scale, *LEIDS* The Leiden Index of Depression Sensitivity, *EQ-5D-5 L* EuroQoL 5 Dimensions 5 Levels, *WAI* Working Alliance Inventory T0 = baseline, T1 = 4 weeks, T2 = 8 weeks, T3 = 16 weeks, T4 = 26 weeks, T5 = 52 weeks

^a^WAI is self-administered by the patient and therapist 4 times during the course of treatment before the start of the treatment sessions

^b^PCL-5 and DERS are self-administered weekly before the therapy session by the patient

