### Moderators and mediators

In line with previous work [40], we will investigate whether treatment effects are affected by baseline characteristics such as PTSD symptom severity, comorbid symptoms, emotional maltreatment and avoidance behavior, using between- and within-group moderation tests. We will calculate a ‘personalized advantage index’ (PAI) [41] and trees for treatment-subgroup interactions (QUalitative INteraction Trees; QUINT) to evaluate which pretreatment characteristics are most discriminating in predicting optimal treatment and differential response to treatments with a combination of predictor variables. This may lead to the development of optimal (personalized) treatment sequences [41–43].

As to mediators, moderately strong evidence exists that between-session habitation and change in post-traumatic cognitions mediate the effects of PE, while mixed evidence exists for emotional engagement, inhibition learning and within-session habituation [44]. Mediators of iPE are yet unknown. With regard to PBT, there is some evidence for the mediating effect of both emotion regulation improvement and therapeutic alliance on PBT outcome [31, 45]. More research on mediators is needed, as the number and quality of the studies are limited [44]. In the current study we will examine all above mentioned mediators.

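### Posttraumatic cognitions are never measured inside the four-week iPE core, so whether they change before symptoms cannot be tested there

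*Protocol article*

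**What the plan says.** Under Moderators and mediators, the Protocol article rates the evidence for between-session habituation and for change in posttraumatic cognitions as moderately strong in PE. It then lists further candidates for PE and for PBT, says "Mediators of iPE are yet unknown", and commits itself: "In the current study we will examine all above mentioned mediators".

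The iPE core consists of "three weekly sessions of 90 min PE for a period of four weeks (12 sessions total"). Two boosters come later, the first a month on and the second a month after that, which brings the count to 14. PE is 16 weekly sessions. PBT is eight weekly STAIR sessions followed by eight weekly PE sessions.

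Table 1 under Instruments lists the PTCI (construct: "Posttraumatic cognitions") at T0 to T5 only, with "T0 = baseline, T1 = 4 weeks, T2 = 8 weeks, T3 = 16 weeks, T4 = 26 weeks, T5 = 52 weeks". Two footnotes add readings during treatment. One gives the WAI four times. The other reads "PCL-5 and DERS are self-administered weekly before the therapy session by the patient". Neither covers the PTCI. SUD and harm expectancies are rated around the exposure exercises themselves.

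**The concern.** A variable can be put forward as a mediator only if it changes before the outcome does. The assessment grid suits a 16-week course, where weeks 4 and 8 fall during treatment. The iPE core is over by week 4. If the PTCI is read only before and at the end of that core, cognitions and symptoms change over one and the same interval, and an association between them says nothing about which came first.

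iPE is the arm whose mechanism the protocol calls unknown, and the protocol expects it to work faster than the other two. If that is right, much of the change in iPE falls in the stretch without a PTCI reading. A comparison of cognitive mediation between iPE and PE would then mix mechanism with spacing of measurement. Table 1 fixes what is collected, so no later choice of mediation model can supply the missing readings.

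**Working it through.** **Inputs**
- iPE: 3 sessions a week for 4 weeks, plus 2 boosters (Intensified prolonged exposure therapy).
- PE: 16 weekly sessions (Prolonged exposure therapy). PBT: 8 + 8 weekly sessions (Phase-based therapy).
- PTCI and CAPS-5: weeks 0, 4, 8, 16, 26, 52 (Table 1).
- PCL-5 and DERS: the same weeks, plus weekly before a session (Table 1, second footnote).
- Assumption: week 0 is the start of treatment. The protocol does not state the origin of the week count.

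**Session counts reproduced.** 3 × 4 = 12 core sessions; 12 + 2 = 14 in total. Both agree with the protocol.

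**PTCI readings strictly inside each course**

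| Course | Weeks | PTCI readings inside | Reading at its end |
|---|---|---|---|
| iPE core | 0–4 | 0 | T1 |
| PE | 0–16 | 2 (T1, T2) | T3 |
| PBT, whole | 0–16 | 2 (T1, T2) | T3 |
| PBT, PE phase only | 8–16 | 0 | T3 |

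**What this allows.** To relate mediator change in one interval to outcome change in the next, at least two consecutive intervals are needed. With r readings there are r − 1 intervals and r − 2 such ordered pairs.
- iPE core: T0, T1, so r = 2, giving 1 interval and 0 ordered pairs.
- PE: T0, T1, T2, T3, so r = 4, giving 3 intervals and 2 ordered pairs.
- PE phase of PBT: T2, T3, so r = 2, giving 0 ordered pairs.

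The weekly PCL-5 does not fill the gap for cognitions, because there is no PTCI reading within the iPE core to set against it.

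**Weekly forms.** PCL-5 and DERS give about 4 readings over 12 iPE core sessions, and 12 / 4 = 3 sessions per reading. PE and PBT give up to 16 readings over 16 sessions, one per session. Both forms are also scheduled at T1 to T5 in every arm, so the series continues after the iPE core.

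**Other listed mediators in iPE.** SUD, rated before, during and after exposure, serves within- and between-session habituation and bears on emotional engagement. Harm expectancies, rated before and after exposure, serve inhibition learning. The WAI gives four alliance readings during treatment. DERS gives weekly readings of emotion regulation. Of the seven candidates named, only cognitions has no reading inside the iPE core.

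**The case against.** The strongest reply is that iPE is a 14-session treatment and the zero depends on taking the core as the window. Homework continues after session 12. If the boosters are counted from the end of the core, T1 and T2 both precede the last session. Change in PTCI from T0 to T1 can be related to change in CAPS-5 from T1 to T2 or later, since both are measured at each of these points. This stands, and it is why the point is confined to the core. That analysis addresses later change, however, and not the response during the 12 sessions.

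A second reply is that PBT is no better off where exposure is concerned: its PE phase lies wholly between T2 and T3. This also stands, so PBT is not a clean comparator, and the clear contrast is with PE.

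Third, the Procedure section says in general terms that questionnaires are completed ahead of therapy sessions, which might mean every session. The Table 1 footnote is the specific rule and says weekly. Neither passage adds the PTCI to the pre-session forms explicitly.

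Finally, mediation is an additional aim, no mediation hypothesis is stated for iPE, and sparing patients forms during demanding weeks is a reasonable trade-off. This limits the weight of the point but does not remove it, because the protocol does promise to examine all the listed mediators.

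A reader might infer three stronger things that the protocol does not support:
- That mediators of iPE cannot be studied at all. Six of the seven candidates have some data during treatment.
- That PCL-5 and DERS end with the iPE core apart from the boosters. Table 1 schedules both to week 52.
- That the comparison of speed of improvement is compromised. CAPS-5 falls on the same calendar weeks in all arms, and PCL-5 is weekly in all arms during weeks 1 to 4. A common calendar grid is what that hypothesis needs.

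**Conclusion.** The point holds in a limited form. Within the iPE core, temporal precedence of posttraumatic cognitions over symptoms cannot be tested: there are 0 PTCI readings inside it, against 2 inside the PE course. What remains for iPE is T0–T1 change in PTCI against later change in CAPS-5 or PCL-5. PCL-5 and DERS have about one third of the per-session resolution they have in PE, which is coarse but workable.

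This rests on counting weeks from the start of treatment. If they run from baseline or randomization, T1 could fall before the core ends for some patients. That would give an unplanned in-core reading at a session number that varies between patients.

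The primary outcome, the effectiveness comparison and the speed-of-improvement hypothesis are not affected. It is an inexpensive improvement to a secondary aim, and it has to be made at data collection.

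**What to change.** In iPE, add the PTCI to the pre-session forms within the core, for example before sessions 5 and 9, with a PCL-5 at the same sessions. Cognitions would then be read after 0, 4, 8 and 12 sessions: 4 readings, 3 intervals and 2 ordered pairs. In PE, weeks 4 and 8 already fall after about 4 and 8 weekly sessions, so nothing need be added there. Leave the calendar assessments unchanged in all arms. One PTCI reading within the PE phase of PBT would close the same gap in that arm (3 readings across the phase, 1 ordered pair). State the origin of the week count.

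If no readings are added, limit the within-treatment claim for PTCI in iPE to T0–T1 change predicting later symptom change, and say so in the analysis section.

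The cost is an amendment and, per iPE patient, two PTCI forms and at most two extra PCL-5 forms at sessions already attended (2 × 50 = 100 PTCI forms at the planned 50 per arm). The drawback is somewhat more questionnaire burden in the intensive weeks. The wording-only alternative costs nothing.

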#### Clinician-rated PTSD symptom severity

PTSD diagnosis and symptom severity are assessed with the Clinical Administered PTSD scale (CAPS-5) [54]. The CAPS-5 has recently been validated for the DSM-5 diagnosis of PTSD and has been translated into Dutch [55]. The CAPS-5 has good correspondence with CAPS-4 (*kappa* = .83) for the diagnosis of PTSD and a high internal consistency (α = .88) and test-retest reliability (*ICC* = .78) for the total severity score [56]. Response to the treatment is defined as an improvement of at least 6 points on the CAPS-5 [57]. Remission is defined as response to treatment, loss of diagnosis and a symptom severity score below 26.

#### Self-reported PTSD symptom severity

Posttraumatic symptom severity is also measured with the PTSD checklist for DSM-5 (PCL-5). The PCL-5 has a high internal consistency (*a* = .94) and test-retest reliability (*r* = .82) [58, 59].

#### Comorbid symptom severity

To measure clinician-rated symptoms that have been proposed to define complex PTSD [28] we use three clinical administered items measuring problems with emotion regulation, interpersonal difficulties and low self-esteem (Complex PTSD items, CPI). Emotion regulation, interpersonal difficulties and self-esteem are also assessed with the Trauma Questionnaire of the International Classification of Diseases, 11th edition (ICD-11) [60]. Additionally, emotion regulation difficulties are measured with the Difficulties in Emotion Regulation Scale (DERS) [61]. Interpersonal problems are measured with the Inventory of Interpersonal Problems (IIP-32) [62, 63] and self-esteem with the Rosenberg Self-Esteem Scale (RSES) [64]. Clinician-rated dissociative symptom severity is measured with the two items about the dissociative subtype of PTSD in the CAPS-5. Also, we will also use a new clinical interview for the Dissociative Subtype in PTSD (DSP-I) [65]. Self-reported dissociative symptom severity is measured with the the Dissociative Experiences Scale (DES) [66] and the Somatoform Dissociation Questionnaire (SDQ) [67].

Comorbid axis-1 disorders (DSM-IV) are measured with the Mini International Neuropsychiatric Interview (MINI) [68]. Depression severity is measured with the Beck Depression Inventory, 2nd edition (BDI-II-NL) [69]. Cognitive reactivity and specifically suicidal reactivity is assessed with the Leiden Index of Depression Sensitivity (LEIDS) [70].

Personality disorders are measured with the Structured Clinical Interview for DSM-IV Personality Disorders (SCID-II) [71].

Moreover, anger, negative cognitions, social support and attentional control are measured using self-report questionnaires State-Trait Anger Scale (ZAV) [72], the Posttraumatic Cognitions Inventory (PTCI) [73, 74] the MOS [75, 76] and the Attentional Control Scale (ACS) [76].

#### Trauma history

The LEC-5 [77, 78] measures any experienced traumatic event and the CTQ (Childhood Trauma Questionnaire) will be used to measure childhood trauma specifically [79, 80].

#### Treatment variables

Prior, during and immediately after (imaginal) exposure, Subjective Units of Distress (SUD) ratings are assessed and prior and after exposure harm expectancies are assessed. Treatment credibility of the three therapies will be checked with the adapted Treatment Credibility Scale [81]. Additionally, the Working Alliance Inventory (WAI) [82–84] will be used to examine therapeutic alliance. The treatment goals of the patients are assessed with an adapted version of the Bern inventory of treatment goals [85].

#### Cost-effectiveness

Quality of Life is measured with the EQ-5D-5 L [86, 87]. The EQ-5D-5 L questionnaire will also be used as cost-effectiveness measurement with the use of the social tariffs of the EuroQol.

Moreover, cost-effectiveness is determined with the Trimbos/iMTA questionnaire for costs associated with Psychiatric Illness (TiC-P) [88] which measures the (in)direct costs of illness (health care use and lost productivity), and is specifically developed for the Dutch Healthcare system.

#### Avoidance task

A classical associative learning paradigm is administered to measure avoidance behaviors. In this task, emotional, anxiety provoking pictures from the International Affective Picture System (IAPS)- set are used as unconditioned stimulus (US), and pictures of an office containing a light, that changes color (blue, red, yellow) as the conditioned stimulus (CS). Participants can avoid the US by pressing a button, but success is dependent on the CS [89].

### Analyses

Data analyses will be based on intention-to-treat analyses. All randomized patients will be included in the analyses. Due to the structured data, we will use multiple imputation of multilevel data which takes the levels within the data into account [90].

Primary and secondary continuous outcome parameters will be analyzed with multilevel mixed models using a repeated measurement design to correct for the dependencies among the observations [91, 92]. Dichotomous secondary outcome parameters will be analyzed with multilevel logistic regression. The intraclass correlation will be determined to give an indication about these dependencies and determine the residuals which can be explained within and between patients [92]. The models will be fitted with the lme4 package in R and with a FML estimation method [93]. The models will be nested, so the models are compared with the likelihood ratio test (LRT) [94]. All assumptions of the models will be checked to ensure the reliability of the results. When major assumptions are violated, clustered bootstrap will be used, since this method can handle structured data and has less stringent assumptions than multilevel models. Cost-utility analysis will be based on patient reports (societal costs per QALY), and cost-calculator spreadsheet model (BIA). The economic evaluation will also be based on analysis to treat; standard Dutch unit prices will be used.

For moderation and mediation analyses, regression based approaches will be used with the PROCESS macro in SPSS [95]. For moderation analyses with multiple time points, linear mixed models will be used with an interaction effect between time and the moderation variable of interest. For between treatment moderation analyses the three-way interaction between the moderator, treatments and time will be calculated. For calculation of the personalized advantage index we will use leave-one-out cross validation to generate the counterfactual prediction per patient using prognostic and prescriptive variables from moderation analyses and generate the PAI, the magnitude of the predicted difference of receiving the predicted optimal treatment versus the non-optimal treatment [41, 96]. For the Trees for treatment-subgroup interactions we will use the R-package quint which uses a stepwise tree building algorithm to detect treatment by subgroup interaction allowing all possible predictor combinations in the model. The algorithm subdivides all patients in terminal nodes based on their patient characteristics and further assigns patients to nodes in which either one of the treatment is better than the other or both treatments are equally effective [42, 43].

## Discussion

Completion of this RCT will provide more knowledge about the relative effectiveness of three treatment strategies for CA-PTSD. We will directly compare the effects of a well-established treatment (prolonged exposure) and two treatment innovations (intensified prolonged exposure and phase-based treatment) in this difficult to treat patient population. Furthermore, cost-effectiveness of the three interventions will be examined. Finally, moderation and mediation analyses will provide more information for whom and under which conditions these treatments are most effective. Ultimately, this might assist clinicians in personalizing treatment indications and optimizing treatment delivery.

### Methodological considerations

We expect to include a cultural and socioeconomic diverse sample, since the participating centers are located in large cities. We protect the generalizability of the findings by using few exclusion criteria. The relatively long follow-up measurements of 6 and 12 months will provide insights in the long-term effects of the therapies. Every type of treatment is supervised by expert supervisors of that specific method. Additionally, all therapists are trained and supervised in both PE and PBT. This prevents biases to the internal reliability of the study and is essential for a meaningful interpretation of the results [39].

Limitations of this study are that not all eligible patients will agree to participate in the study which could result in selection bias. Especially the iPE condition could lead to selection bias since it is more demanding in terms of time investment in the first weeks of the treatment. All reasons of patients to decline participation in the study will be carefully monitored to ensure the generalizability of the results and for implementation purposes. Another limitation is that patients have one therapist in PE and PBT, but two alternating therapists in the iPE condition. This may influence the therapeutic alliance and consequently the results of the treatment. We will assess whether therapeutic alliance indeed differs between condition and, if so, whether this has any influence on treatment results.

